## Abstract

Stimulation of the vagus nerve, a parasympathetic nerve that controls the neuro-digestive, vascular, and immune systems, induces pain relief, particularly in clinical conditions such as headache and rheumatoid arthritis. Transmission through vagal afferents towards the nucleus of the solitary tract (NST), the central relay nucleus of the vagus nerve, has been proposed as the main physiological mechanism that reduces pain intensity after vagal stimulation. Chronic pain symptoms of fibromyalgia patients might benefit from stimulation of the vagus nerve via normalization of altered autonomic and immune systems causing their respective symptoms. However, multi-session non-invasive vagal stimulation effects on fibromyalgia have not been evaluated in randomized clinical trials. We propose a parallel group, sham-controlled, randomized study to modulate the sympathetic–vagal balance and pain intensity in fibromyalgia patients by application of non-invasive transcutaneous vagus nerve stimulation (tVNS) over the vagal auricular and cervical branches. We will recruit 136 fibromyalgia patients with chronic moderate to high pain intensity. The primary outcome measure will be pain intensity, and secondary measures will be fatigue, health-related quality of life, sleep disorders, and depression. Heart rate variability and pro-inflammatory cytokine levels will be obtained as secondary physiological measures. We hypothesize that multiple tVNS sessions (five per week, for 4 weeks) will reduce pain intensity and improve quality of life as a result of normalization of the vagal control of nociception and immune–autonomic functions. Since both vagal branches project to the NST, we do not predict significantly different results between the two stimulation protocols.

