Considering that the vagus nerve controls pain signals towards the central nervous system [14,19,20], and growing evidence of autonomic dysfunction in fibromyalgia in terms of sympathetic hyperactivity [21,22,23,24,25,26,27], it can be argued that rebalancing the sympathetic–parasympathetic activity via vagal stimulation might reduce the intensity of pain and stabilize the autonomic symptoms of this disease. In addition, an immune system alteration [28] seems to mediate the interaction between the autonomic nervous system and the chronic inflammatory state in fibromyalgia, apparently by the influence of inflammatory cytokines and chemokines [28,29,30]. This well-described inflammatory state in fibromyalgia patients is critically important for treatment approaches. Auricular and cervical vagus nerve stimulation might reduce such inflammatory overactivity as well via efferent modulation of the activity of the spleen and inflammatory processes [18] and hereby reduce pain symptoms [19]. In accordance, invasive vagal nerve stimulation has been shown to be effective in treatment-resistant fibromyalgia patients, with a tolerability profile similar to that described for the treatment of epilepsy and depression [31]. However, to the best of our knowledge, the potential of non-invasive auricular and cervical vagus nerve stimulation under repeated sessions to improve fibromyalgia symptoms has not been evaluated in randomized, sham-controlled clinical studies. Auricular and cervical transcutaneous vagus nerve stimulation (tVNS), two non-invasive low-intensity electric stimulation procedures [32,33], have however been explored with respect to their potential to modulate the activity of this nerve in other clinical settings [20,34,35,36,37], and the effectiveness of these non-invasive methods might not differ significantly from those of invasive stimulation, while non-invasiveness provides an advantageous safety profile [14,19,38,39,40]. 

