## 2. Materials and Methods

### 2.1. Participants

Adult fibromyalgia patients, in an age range between 18 and 69 years, recruited from the Hospital Juan Ramón Jiménez of Huelva, Spain, will be interviewed to voluntarily participate in this monocentric study. Inclusion criteria will be the diagnosis of fibromyalgia by a physician, based on the 2010 American College Rheumatology (ACR) fibromyalgia diagnostic criteria, and the maintenance of characteristic symptoms for more than a year. A moderate to high pain intensity according to analog pain scales (above 4 points over 10), maintained for more than 6 months, will also serve as an inclusion criterion. The usual individual medical treatment for fibromyalgia will be maintained throughout the study, including psychopharmacological treatments. All genders will be included. Exclusion criteria will include standard conditions to be considered for VNS (cardiac arrhythmia, sleep apnea, pregnancy, etc.) [49], other chronic diseases producing widespread pain not related to known symptoms of fibromyalgia, multiple pharmacological treatments for symptoms different from those of fibromyalgia, primary psychiatric syndromes (psychosis, bipolar disorder, etc.) with or without treatment via central nervous system-acting medication, drug dependence (including smoking), vagal syndrome or history of vagal symptoms, and chronic pain and fibromyalgia secondary to inflammatory rheumatic diseases. Previous interventions with non-invasive brain stimulation methods or invasive VNS will also constitute exclusion criteria. An electrocardiogram will be performed in all participants before the study. Participants with arrhythmia and other cardiac alterations will be excluded from the study.

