*L* device. A technical variant of this device, in which the original connector is modified to incorporate self-adhesive electrodes, will be used for cervical vagal stimulation and axillary nerve stimulation (the latter as an added control group). Thus, stimulation over the cervical branch of the vagus nerve and axillary nerve stimulation will be applied by adapted electrodes for transcutaneous stimulation outside the ear (Figure 1). In order to effectively access cervical vagal projections, as reported in previous studies [36], 2 cm^2^ self-adhesive anodal and cathodal electrodes will be used for cervical vagal stimulation. These adapted electrodes will also be used in the active control group with axillary nerve stimulation (Figure 2). Since efferent fibers of the vagus nerve controlling cardiac functions are mainly located in the right branch [51], but no arrhythmic effects have been reported after left transcutaneous vagus nerve stimulation [52], tVNS will be applied over the left branch for safety reasons. For sham auricular tVNS, the anodal electrode will be placed over the center of the left ear lobe as previously reported [53], because there is no vagal innervation around the ear lobe [54] and stimulation of this area does not alter brain activity, including the brain stem [55]. The cathode will be placed over the antitragus. (Figure 2A). Accordingly, in the sham cervical tVSN protocol, the anodal electrode will be placed 2 cm anterior to the cervical branch of the vagus nerve, and the cathode below the cheek (Figure 2B). This method and these stimulation parameters have been previously used for reliable blinding in other clinical studies [56]. Series of electrical pulses with 250 μs pulse width, 25 Hz frequency, and 28 s inter-burst interval (32 s on/28 s off duty cycle) will be applied in each intervention session to induce effective vagal stimulation and avoid stimulation habituation. Auricular tVNS will be applied at 1mA intensity for 30 min per session (1 session per day, 5 consecutive days a week, 20 sessions in total). In order to reach equivalent current density as for the auricular electrodes, which include a maximum contact area of 1 cm^2^, the stimulation intensity for non-auricular electrodes (2 cm^2^) will be adjusted to 2 mA, which will allow achieving comparable current densities at the electrode–skin interface for the respective electrode sizes. The other non-auricular stimulation parameters will remain the same as for the auricular stimulation protocol.

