### 2.5. Procedure

The patients will be recruited according to the inclusion and exclusion criteria. Then, only patients without alterations in the electrocardiogram will be randomly assigned to one of five groups: auricular vagus nerve stimulation at 25 Hz frequency (atVNS) (*n* = 34); sham auricular vagus nerve stimulation (Sham atVNS) (*n* = 17); cervical vagus nerve stimulation at 25 Hz frequency (ctVNS) (*n* = 34); sham cervical vagus nerve stimulation (Sham ctVNS) (*n* = 17); axillary nerve stimulation at 25 Hz frequency (ANS) (*n* = 34). Pre-intervention baseline measures (FIQR, BPI, PSQI, and BDI) will be performed once a week for 3 weeks and before the first intervention day, resulting in four baseline measures (one per week) to evaluate the stability of the symptoms. Then, each participant will receive five 30 min consecutive sessions of stimulation (verum or sham) per week (one per day), for four weeks (in total, 20 sessions) over the left branch of the auricular or cervical vagal nerve or over the left axillary nerve, depending on the group. The patients will not be aware of the stimulation condition (verum vs. sham) within each group, and data analyses will be conducted by researchers not involved in the respective interventions, who will use numerical codes for each experimental condition in order to assure double blinding. Once the analyses have been conducted, the codes will be revealed. In the atVNS verum and sham groups, the anodal electrode will be positioned over the cymba conchae of the left auricle and the center of the left ear lobe, respectively, and the cathode (return electrode) over the antitragus. In the ctVNS verum group, the anodal electrode will be positioned on the surface of the throat that corresponds to the position of the left cervical branch of the vagus nerve, adjacent to the position of the cervical carotid artery (2 cm anterior to this branch for the sham ctVNS condition), and the cathode over the lower cheek. In the ANS verum group, the anode will be positioned over the left axillary nerve under the shoulder, and the cathode over the lower cheek. The positions of the electrodes for the respective procedures are shown in Figure 2.

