The post-baseline outcome measures (FIQR, BPI, PGIC, PSQI, and BDI) will be recorded immediately after the fifth session of each intervention week, resulting in four intra-intervention measurements. Four additional post-intervention follow-up measures will be recorded to evaluate potential short- and long-lasting treatment effects, a week, a month, 3, and 6 months after the last intervention session, resulting in four intra-intervention and four post-intervention measurements. Although no conclusive evidence about tVNS effects on heart rate variability is available [69], heart frequency will be recorded before and after each tVNS session, the high-frequency/low-frequency heartbeat ratio will be calculated, and data will be correlated with the outcome measures. Pro-inflammatory cytokine levels taken from blood samples before the start of the intervention and immediately after 10 and 20 intervention sessions, as well as 1 week, and 1 month after the end of the intervention, will be analyzed as proposed biomarkers of the anti-inflammatory effects of the intervention [70]. To measure plasma cytokine levels, the enzyme-linked immunosorbent assay (ELISA) protocol will be used [71]. Plasma collection will be selected to optimize the yield of cytokines of interest (TNF α, IL-1β, IL-6) [72]. Within 1 h after collection, blood will be centrifuged for 10 min at 1300 g and 4 °C, and the supernatant will be transferred to a separate tube and then centrifuged for 10 min at 16,000 g and 4 °C. The resulting platelet-poor plasma will be stored in 0.5 mL aliquots at low temperatures (−80 °C) in order to maintain cytokine stability until the analysis. After each intervention, participants will be asked to guess the stimulation condition (real, sham, or unable to guess) for evaluation of successful blinding as previously reported [73], and any adverse effect of the stimulation or any aspect related to tVNS will be evaluated via an adapted standard questionnaire for assessment of adverse effects induced by a related non-invasive brain stimulation tool, namely, transcranial direct current stimulation (tDCS) [74], as a measure of the safety of the intervention. All sessions will take place at the aforementioned hospital. Figure 3 depicts the design of the study.

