## 3. Discussion

This study aims to explore the effects of multiple tVNS sessions on fibromyalgia symptoms. Because the vagus nerve modulates afferent pain signals to the central nervous system and the tone of the autonomic, immune, and emotional systems [19], the application of tVNS, a non-invasive low-intensity electric stimulation technique with potential to activate A- and B-fibers [75], might normalize the functions of vagal afferences, which seem to be pathologically altered in fibromyalgia [25], and thus reduce the characteristic symptoms of this disease, particularly muscular and generalized pain. Encouraging results have been reported for invasive vagal stimulation procedures in fibromyalgia treatment [31], but controlled clinical trials using non-invasive vagal stimulation are missing with respect to the effectiveness and safety of this neuromodulation option. The proposed study might shed light on the involvement of vagal activity and sympathetic–vagal balance in chronic pain and other symptoms of patients with fibromyalgia and also provide direct comparisons between two tVNS protocols in terms of effectiveness and safety. In particular, we hypothesize that this protocol of vagal neuromodulation is effective and safe for improving pain and other symptoms in these patients. The inclusion of a sham intervention condition is important to demonstrate the specificity of the therapeutic effectivity of this intervention. The inclusion of an active control condition, in which a nerve not related to fibromyalgia symptoms (the axillary nerve) is stimulated, will deliver further evidence about the specificity of the effects. The high number of intervention sessions (20 sessions, over 4 weeks) included in this stimulation protocol might serve to control for null effects of tVNS due to under-dosing.

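### The prior-treatment exclusion names invasive VNS and brain stimulation but not earlier non-invasive VNS, so as written it can admit patients already treated with the trial's own intervention

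*Protocol article*

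**What the plan says.** The prior-treatment rule is one sentence in section 2.1 (Participants): "Previous interventions with non-invasive brain stimulation methods or invasive VNS will also constitute exclusion criteria". The other VNS-related exclusion in that section concerns medical conditions, not exposure: "Exclusion criteria will include standard conditions to be considered for VNS (cardiac arrhythmia, sleep apnea, pregnancy, etc".

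The Abstract gives the intervention under test as "application of non-invasive transcutaneous vagus nerve stimulation (tVNS) over the vagal auricular and cervical branches". The Introduction says of the auricular and cervical forms that they "have however been explored with respect to their potential to modulate the activity of this nerve in other clinical settings", so earlier exposure is possible.

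On blinding, section 2.5 (Procedure) says: "The patients will not be aware of the stimulation condition (verum vs. sham) within each group". Section 2.2 sets the auricular sham by electrode site: "For sham auricular tVNS, the anodal electrode will be placed over the center of the left ear lobe". Active auricular treatment has the anode on the cymba conchae. The cervical sham moves the anode 2 cm forward of the nerve. The primary outcome, in section 2.3, is pain reported by the patient on the BPI.

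**The concern.** The exclusion appears meant to keep out people with experience of neuromodulation. It names two categories, and the exposure closest to the trial treatment is in neither by name. A site that applies the sentence literally would reject a former tDCS patient and could accept a former tVNS patient.

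Two things are at stake. First, blinding within the auricular and cervical pairs depends on the patient not knowing which site is the active one. Someone who has worn a real electrode at that site may know, and the outcome is the patient's own rating. Second, a previously treated patient may arrive with a residual effect, or with expectations formed by having responded or not responded before.

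**Working it through.** **1. Scope of the sentence.** The relevant places, side by side:

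| Earlier exposure | Covered by 2.1? |
|---|---|
| tDCS or other non-invasive brain stimulation | Yes, named |
| Implanted VNS | Yes, named as invasive VNS |
| Auricular or cervical tVNS | Not named. Covered only if tVNS counts as brain stimulation |

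Section 2.1 lists VNS apart from brain stimulation and restricts it with the word invasive. The Discussion describes "tVNS, a non-invasive low-intensity electric stimulation technique with potential to activate A- and B-fibers". Neither there nor in the Introduction is tVNS classed as brain stimulation. The nearest the article comes is in section 2.5, where the safety questionnaire is adapted from one for "adverse effects induced by a related non-invasive brain stimulation tool, namely, transcranial direct current stimulation (tDCS". The word related links the two techniques but does not say that tVNS belongs to that class.

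**2. Consistency with the article's own reasoning.** The Introduction suggests that non-invasive stimulation may be about as effective as invasive stimulation. Section 2.5 follows patients to 6 months to look for lasting effects. If earlier invasive VNS is a reason to exclude, the same reasoning covers earlier tVNS.

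**3. Size in the sham group.** Section 2.5 plans groups of 34, 17, 34, 17 and 34. The sample-size text in 2.1 pools the two shams, and section 2.6 analyses four groups, so the analysed sham group is 17 + 17 = 34.

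- One patient: 1/34 = 2.9%. Two patients: 2/34 = 5.9%.
- Under the planned sizes, expecting one such patient in pooled sham requires 136/34 = 4 experienced recruits in the whole trial. Expecting two requires 8.
- Recognition by site needs exposure at the same site. A former auricular user has a chance of (34 + 17)/136 = 37.5% of being placed in either auricular arm, and 17/136 = 12.5% of being placed in its sham.

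**4. Sample size.** Inputs from 2.1: f = 0.2, alpha = 0.05, 4 groups, 2 measurements, correlation 0.5, nonsphericity 1.

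- Non-centrality: f² × N × m/(1 − ρ) = 0.04 × 112 × 2/0.5 = 17.92, as stated.
- Degrees of freedom: 3 × 1 = 3 and (112 − 4) × 1 = 108. Critical F is 2.689 (stated 2.68) and power is 0.9513 (stated 0.951).
- Dropout allowance: 28 × 1.2 = 33.6, so 34 per group and 136 in total, as stated.

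The plan's figures reproduce, and naming tVNS in the exclusion changes none of these inputs.

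**5. Illustration only.** The documents give no share of previously treated patients. Assume a share q who contribute no group difference, so that f becomes 0.2 × (1 − q), with N = 112:

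| q | f | Non-centrality (448 × f²) | Power |
|---|---|---|---|
| 0% | 0.200 | 17.92 | 0.951 |
| 2% | 0.196 | 17.21 | 0.943 |
| 5% | 0.190 | 16.17 | 0.928 |
| 10% | 0.180 | 14.52 | 0.896 |

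This covers dilution only. Recognising sham could instead widen the apparent difference, and no power figure describes that bias.

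**The case against.** The strongest reply is that the authors regard tVNS as a form of non-invasive brain stimulation. Section 2.5 calls tDCS a related tool, section 2.2 defends the ear-lobe sham by its lack of effect on brain activity, and the Introduction describes cortical effects of vagal stimulation. On that reading, invasive VNS was added only because an implant would not otherwise be covered. The reading is possible, but the article never states it. What stands is that the wording may be ambiguous rather than a definite gap. The remedy is the same in either case.

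Other features limit the harm. Entry requires pain above 4 out of 10 for more than 6 months, which makes a strong residual benefit less likely. Four weekly baseline measures check stability. Patients guess their condition after each intervention, and section 2.6 tests those guesses. Randomisation balances earlier exposure in expectation. These points stand as mitigation, but they reveal recognition of sham in part and do not prevent it. The baseline comparisons in section 2.6 cover scores, gender, age and education, not earlier tVNS.

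A fuller protocol may also contain the missing words, since the article condenses it. However, this sentence states a rule with a defined boundary, and the boundary is what is at issue.

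**Conclusion.** The point holds as a modest flaw in a stated eligibility rule. As written, the rule can admit patients previously treated with tVNS, and at best it leaves their status unclear. The risk to blinding and to baseline is plausible, not demonstrated. Its size depends on how many recruits have had tVNS. The documents do not say, and the number is probably low: recruitment is at one hospital, and the Introduction knows of no randomised, sham-controlled study of repeated tVNS in fibromyalgia.

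Three stronger readings are tempting and are not supported:

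- A reader might set one or two patients against a single sham arm of 17 and get 6% to 12%. The analysis pools the shams, so the relevant share is about 3% to 6%.
- A reader might infer that the trial would no longer test its intended question. The Introduction states the objective for fibromyalgia patients in general, not for patients new to VNS, and a few experienced patients would not change it.
- A reader might say the article itself sets tVNS apart as peripheral stimulation. It does not use that term for tVNS. The case rests on how 2.1 is worded.

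**What to change.** Reword the sentence in section 2.1 so that it excludes any previous vagus nerve stimulation, whether invasive or non-invasive (auricular or cervical), alongside previous non-invasive brain stimulation. Add one question on this to the screening interview. The cost is one phrase, one question and possibly a few more screen failures. The sample size and analysis do not change.

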### 2.2. tVNS

Auricular vagal stimulation will be performed by the tVNS^®^
*L* device (tVNS Technologies GmbH, Erlangen, Germany, https://u.pcloud.link/publink/show?code=kZ0mYfXZRXxQqurVY9SB8okpGtAc55aX7nrX, accessed on 28 December 2021). tVNS^®^
*L* is a battery-driven electrical stimulator connected to an ear electrode which is positioned over the skin of the cymba conchae (Figure 1). Thus, auricular vagal stimulation will be applied using the typical ear electrodes of the tVNS^®^
*L* device. A technical variant of this device, in which the original connector is modified to incorporate self-adhesive electrodes, will be used for cervical vagal stimulation and axillary nerve stimulation (the latter as an added control group). Thus, stimulation over the cervical branch of the vagus nerve and axillary nerve stimulation will be applied by adapted electrodes for transcutaneous stimulation outside the ear (Figure 1). In order to effectively access cervical vagal projections, as reported in previous studies [36], 2 cm^2^ self-adhesive anodal and cathodal electrodes will be used for cervical vagal stimulation. These adapted electrodes will also be used in the active control group with axillary nerve stimulation (Figure 2). Since efferent fibers of the vagus nerve controlling cardiac functions are mainly located in the right branch [51], but no arrhythmic effects have been reported after left transcutaneous vagus nerve stimulation [52], tVNS will be applied over the left branch for safety reasons. For sham auricular tVNS, the anodal electrode will be placed over the center of the left ear lobe as previously reported [53], because there is no vagal innervation around the ear lobe [54] and stimulation of this area does not alter brain activity, including the brain stem [55]. The cathode will be placed over the antitragus. (Figure 2A). Accordingly, in the sham cervical tVSN protocol, the anodal electrode will be placed 2 cm anterior to the cervical branch of the vagus nerve, and the cathode below the cheek (Figure 2B). This method and these stimulation parameters have been previously used for reliable blinding in other clinical studies [56]. Series of electrical pulses with 250 μs pulse width, 25 Hz frequency, and 28 s inter-burst interval (32 s on/28 s off duty cycle) will be applied in each intervention session to induce effective vagal stimulation and avoid stimulation habituation. Auricular tVNS will be applied at 1mA intensity for 30 min per session (1 session per day, 5 consecutive days a week, 20 sessions in total). In order to reach equivalent current density as for the auricular electrodes, which include a maximum contact area of 1 cm^2^, the stimulation intensity for non-auricular electrodes (2 cm^2^) will be adjusted to 2 mA, which will allow achieving comparable current densities at the electrode–skin interface for the respective electrode sizes. The other non-auricular stimulation parameters will remain the same as for the auricular stimulation protocol.
